#### Wait-list control

2.4.2

The control group will be assigned to WLC and will receive no treatment for the first six weeks. Considering ethical equity, the control group will undergo the same MQT-SH over the next six weeks.

### Sample size

2.5

The sample size was estimated using G*power (37). The sample size calculation is based on a power of 80% and a type I error of 5%, as well as a moderate effect size for the intervention (partial *η*^2^ = 0.04). A minimum sample size of 25 participants per group is estimated (50 participants in total). This number was obtained by performing a simulation procedure using repeated-measures ANOVA, considering the existence of a significant 2 (group: experimental *vs*. control) × 2 (time: T1 *vs*. T2) interaction effect. Considering a dropout rate of 20%, we aim to include 32 participants per group (64 participants in total).

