### Randomization

2.6

Participants will be randomly allocated to either the experimental or the control group (1:1 ratio, block size = 4). Random numbers for allocation will be generated by the computer and managed by the researcher ([name]). Before enrollment, the participants and other researchers will be unaware of the allocation. After enrollment, [name] will allocate participants to the experimental or control group according to random numbers, and the results of the allocation will be shared only with the clinical research coordinator.

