### Statistical analyses

2.13

Analyses based on the Intention-To-Treat (ITT) principle will be conducted, with missing data imputed using expectation-maximization (EM) algorithm.

To investigate the effect of MQT-SH, 2 (group: MQT-SH *vs*. WLC) × 2 (time: T1 *vs*. T2) repeated measures ANOVA will be performed. If the interaction between the group and time is significant, a simple main effect analysis will be performed.

Additional analyses will be performed. First, to investigate the follow-up effect of the MQT-SH, a paired t-test will be performed to compare T3 and T1 and T3 and T2 in the experimental group alone. Second, a paired t-test comparing T3 and T2 in the control group will be performed to investigate the effects of MQT-SH. Third, a subgroup analysis will be performed to investigate the difference in effectiveness depending on the amount of home training. For this purpose, 2 (amount: top 30% *vs*. bottom 30%) × 2 (time: pre-intervention *vs*. post-intervention) repeated-measures ANOVA will be performed. Data from both the experimental and control groups will be used for subgroup analysis.

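### Section 2.5 pairs 80% power at 25 per group with a moderate effect of partial η² = 0.04, but on the scale of the planned interaction test 25 per group reach 80% power only at 0.81 SD of change (partial η² about 0.14)

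*Protocol article*

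**What the plan says.** Section 2.5 (Sample size) of the protocol article names the software: "The sample size was estimated using G*power (37"). The calculation is "based on a power of 80% and a type I error of 5%, as well as a moderate effect size for the intervention", the effect being given as partial η² = 0.04. The result is stated as "A minimum sample size of 25 participants per group is estimated (50 participants in total"), and the method as follows: "This number was obtained by performing a simulation procedure using repeated-measures ANOVA", for the 2 × 2 group-by-time interaction. A 20% dropout allowance raises this to 32 per group, 64 in total.

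Section 2.13 (Statistical analyses) plans the same test, group by "2 (time: T1 *vs*. T2) repeated measures ANOVA will be performed", and Section 3 calls the T1–T2 comparison the main analysis. The article states no T1–T2 correlation, no effect-size convention, and no target difference in scale points or SD units.

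**The concern.** The test that is powered and the test that is planned are the same 1-df interaction. A reader will therefore take the 0.04 in Section 2.5 to be the partial η² that this ANOVA reports. On that reading the four stated items (80%, moderate, 0.04, 25 per group) do not fit together: an effect of that size needs far more than 50 participants.

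What is at stake is how the result is read. If the trial is believed to have 80% power for a modest effect, a non-significant interaction may be taken as evidence against such an effect, although the design had a low chance of detecting it.

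**Working it through.** **Inputs.** From Section 2.5: power 80%, α = 5%, partial η² = 0.04, 25 per group, dropout 20%. From Section 2.6: 1:1 allocation. The 1-df interaction F test is equivalent to a two-sided two-sample t test on the T2 − T1 change. Assumed: equal SD σ at T1 and T2, and a T1–T2 correlation ρ, which the article does not give.

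**1. Reproducing the plan's figure.** f² = 0.04/(1 − 0.04) = 0.0417, so f = 0.204. G*Power's default within-between convention uses λ = N·f²·m/(1 − ρ), with m = 2 time points. At ρ = 0.5 and N = 50, λ = 50 × 0.0417 × 2/0.5 = 8.33. With F(1, 48) the power is 80.75%, and 50 is the smallest N that reaches 80%. Dropout: 25/0.8 = 31.25, rounded up to 32 per group. Both stated figures reproduce.

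**2. The effect this N is powered for.** Under that convention f is the SD of the four interaction cell effects divided by σ. In a 2 × 2 design a difference in change δ puts ±δ/4 in each cell, so δ = 4fσ = 0.82σ. The SD of change is σ√(2(1 − ρ)), which equals σ at ρ = 0.5, so this is also 0.82 SD of change. The partial η² of the tested interaction is (λ/N)/(1 + λ/N) = 0.1667/1.1667 = 0.143, not 0.04.

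**3. Power if 0.04 is the partial η² of the tested interaction.** The difference is d = 2f = 0.41 SD of change, and λ = f²·N, or f²·(N − 2) on the alternative convention.
- N = 50: λ = 2.08 or 2.00, power 29.3% or 28.3%.
- N = 64: power 36.3% or 35.3%.
- Total N for 80% power: 192 or 194.

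**4. A check that needs no ρ and no convention.** The observed partial η² is F/(F + 48) when N = 50. An observed value of exactly 0.04 gives F = 0.0417 × 48 = 2.0, p ≈ 0.16. Significance at 5% needs an observed value of at least 0.078 (0.061 with 64). A test cannot have 80% power for an effect that is not significant when it is observed exactly.

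**5. What 25 per group detect.** With λ = (n/2)d² and F(1, 48), 80% power needs λ = 8.175. So d = √(8.175/12.5) = 0.81 SD of change, and partial η² = (d²/4)/(1 + d²/4) = 0.1635/1.1635 = 0.14. With 32 per group, d = 0.71. For d = 0.5 SD of change, power is 41% with 25 per group and 50% with 32; 80% would need 64 per group.

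**6. Dependence on ρ.** The 0.81 in SD of change does not depend on ρ. Its raw-score equivalent is 0.81 × √(2(1 − ρ)). The last column enters f = 0.204 under G*Power's convention.

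| ρ | 0.81 SD of change, in raw-score SD | Power at N = 50, G*Power convention |
|---|---|---|
| 0.3 | 0.96 | 67% |
| 0.5 | 0.81 | 81% |
| 0.7 | 0.63 | 95% |
| 0.8 | 0.51 | 99% |

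**The case against.** The strongest reply is that the sample size is correct for the software named. With G*Power's default convention and ρ = 0.5, an entry of 0.04 gives exactly 50, and the dropout inflation is right. This stands: a reader might infer an arithmetic error, and the calculation does not support that. What fails is the meaning attached to 0.04.

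A journal article may also leave the correlation to the full protocol. That stands too, so the missing ρ is not the point. The simulation inputs are not shown, and 0.5 is only the value that reproduces 50. Sensitivity to ρ runs both ways: power on the software's convention is lower than stated at 0.3 and higher at 0.7.

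A reader might also infer that the trial can detect only a large effect. In SD of change the detectable difference is 0.81. In raw-score SD it falls to 0.63 at ρ = 0.7 and 0.51 at ρ = 0.8, and the article does not say what ρ is. Large on the raw scale is therefore not established.

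Nor is it established that any moderate benefit would more likely than not be missed. The 41% applies to 0.5 SD of change with 50 completers. With all 64 observed it is 50%, and a raw difference of 0.5 SD has 61% power at ρ = 0.7 and 78% at ρ = 0.8 with 25 per group. Against this, Section 2.8 stops assessing participants who drop out, and imputing their values does not restore the information of 64 observed participants.

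Finally, nothing in the article commits the authors to reading a null result as proof of no effect. That is a risk, not a stated plan.

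**Conclusion.** The concern holds as a misdescription of the detectable effect. On the scale of the trial's own interaction test, partial η² = 0.04 has about 29% power at N = 50 and 36% if all 64 supply data, and 80% power would need about 192 to 194 in total. With 25 per group, 80% power is reached at 0.81 SD of the change score, an interaction partial η² of about 0.14. These figures hold whatever the T1–T2 correlation. Only the reproduction of 50 and the raw-score equivalents depend on it. The conclusion rests on reading 0.04 as the partial η² of the planned test, which is the natural reading because Sections 2.5 and 2.13 name the same 2 × 2 interaction. It does not show that the N was miscalculated, or that the trial is limited to large effects on the raw scale.

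**What to change.** Keep 64 and restate Section 2.5 along these lines: *25 completers per group give 80% power (two-sided 5%) for a between-group difference in T1–T2 change of 0.81 SD of the change score (interaction partial η² about 0.14); power for 0.5 SD of change is 41%.*

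Delete the word moderate and the 0.04, or label the 0.04 as the input under G*Power's convention and give the correlation actually entered. Do not attach a correlation to the SD-of-change figure, which does not need one. Give a raw-score equivalent only together with its correlation. Add that a non-significant result will be interpreted through its confidence interval.

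The cost is wording only: sample size, analysis and conduct are unchanged, which suits a trial that Section 3.3 reports as already recruiting and treating. The price is a less favourable stated detectable effect.

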### Randomization

2.6

Participants will be randomly allocated to either the experimental or the control group (1:1 ratio, block size = 4). Random numbers for allocation will be generated by the computer and managed by the researcher ([name]). Before enrollment, the participants and other researchers will be unaware of the allocation. After enrollment, [name] will allocate participants to the experimental or control group according to random numbers, and the results of the allocation will be shared only with the clinical research coordinator.

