### Eligibility criteria

2.3

Participants will be included if they i) have simultaneously been diagnosed with Hwabyung and depressive disorder by the Hwa-Byung Diagnostic Interview Schedule (HBDIS) (2) and Structured Clinical Interview for DSM-5 (SCID-5) (31); ii) are ≥ 19 years of age; and iii) can participate in the study by considering the timetable.

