The MQT-SH period may vary depending on the setting (9). A manual for researchers and participants was developed to improve compliance to the intervention protocol. In this study, the MQT-SH will be conducted once a week for 1.5 h for a total of six weeks. Each session will consist of 20 min of education, 40 min of practice (i.e., meditation), and 30 min of group activities, such as checking home training and sharing practice experiences. This intervention will be conducted as a group program, with a maximum of 12 people per group. Participants will be asked to perform home training five times a week for at least 30 min each day. Participants will receive guided audio materials for home training. Dropouts will be defined as i) individuals attending three or less out of six sessions, ii) those who complain of physical or psychological discomfort and want to give up because of such discomfort, or iii) those who would want to give up for reasons other than discomfort.

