### Blinding

2.7

In this clinical trial, assessors will be blinded. However, participants and practitioners will not be blinded. The assessors will be blinded to the intervention group and prevented from speaking with the participants, except during the clinical interviews.

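### A single fixed, published block size of 4 lets up to one allocation in three be deduced in advance, so the stated concealment is not secured

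*Protocol article*

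**What the plan says.** All references are to the protocol article.

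- **Section 2.6, Randomization.** The scheme is "1:1 ratio, block size = 4", with no strata stated. On custody of the list: "Random numbers for allocation will be generated by the computer and managed by the researcher". The same researcher allocates participants after enrolment. On concealment: "Before enrollment, the participants and other researchers will be unaware of the allocation". On release of results: "the results of the allocation will be shared only with the clinical research coordinator".
- **Section 2.7, Blinding.** Assessors are blinded, but "participants and practitioners will not be blinded".
- **Section 2.3, Eligibility criteria.** Two diagnoses by named interviews, a minimum age, and a third criterion that the person "can participate in the study by considering the timetable".
- **Sections 2.1 and 2.4.** MQT-SH is given in weeks 1-6 to the experimental arm and in weeks 7-12 to the wait-list arm, in classes "with a maximum of 12 people per group".
- **Sections 2.2 and 3.1.** One hospital, hence one allocation list.
- **Section 3.3, Trial status.** Recruitment, enrolment and treatment have begun.

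**The concern.** Concealment has to hold for the next participant, not only for the list as a whole. With every block of length 4 and balanced, the fourth allocation always follows from the first three, and the third follows from the first two whenever those match. The block size is in print, and at least two people (the list holder and the coordinator) know the results. The sentence that other researchers do not know the allocation before enrolment is therefore only as good as the separation between those two people and the decision to enrol.

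If someone who can foresee the next arm also judges eligibility, the third criterion leaves room for discretion. It has no stated threshold, and class times differ by arm. Accepting or deferring a candidate according to availability or motivation would then be selection at entry. Blinded assessment at T2 does not correct that, and a baseline comparison only partly reveals it. It would act on the T1-T2 group comparison, which is the main analysis.

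**Working it through.** **Inputs.** Ratio 1:1 and block size 4 (section 2.6). Target 64 participants (section 2.5): 25/(1 - 0.20) = 31.25, rounded up to 32 per arm, which is 16 blocks of 4. The article gives no figure for predictability, so there is none to reproduce.

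**Certain predictions, one-by-one allocation, observer knows the block size and all preceding allocations.** A balanced block of 4 has 6 equally likely sequences.

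- First and second allocations: never certain.
- Third: certain when the first two match, probability 2/6 = 1/3.
- Fourth: always certain.
- Expected certain allocations per block: 1 + 1/3 = 4/3. Share: (4/3)/4 = 33.3%. Over 16 blocks: 16 x 4/3 = 21.3 of 64.

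**Best-guess hit rate.** By position: 1/2, 2/3, then (1/3)(1) + (2/3)(1/2) = 2/3, then 1. The mean is (1/2 + 2/3 + 2/3 + 1)/4 = 70.8%, against 50% with no information.

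**Lower end.** If all members of a block are enrolled before any of its allocations is released, nothing can be foreseen: 0%. The range is 0-33%.

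**Possible bias.** Suppose candidates placed in predictable MQT-SH slots differ in expected change by +d, and those in predictable wait-list slots by -d. By symmetry, predictable slots are one third of each arm, so the arm means shift by +d/3 and -d/3, a difference of 2d/3. The article gives no basis for d. For assumed d of 0.1 to 0.3 SD, 2d/3 = 0.07 to 0.20 SD. This requires every predictable slot to be steered, always in the same favourable direction. It is therefore the worst case for each d, and the lower end is zero.

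**What other schemes achieve for the same observer.** Fixed blocks were enumerated. Varying blocks were simulated (64 participants, 1,500 runs), with the observer knowing the possible sizes but not their order.

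| Scheme | Certain | Best guess |
|---|---|---|
| Fixed 4 | 33.3% | 70.8% |
| Fixed 6 | 25.0% | 68.3% |
| Fixed 8 | 20.0% | 66.6% |
| Random 4/6 | 5.5% | 69.1% |
| Random 4/6/8 | 2.1% | 67.8% |

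Varying the block size removes most certain predictions but hardly changes the best-guess rate. Keeping knowledge of past allocations away from whoever enrols therefore matters more than the choice of block sizes.

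**The case against.** The case for the plan is substantial. A fixed block of 4 is an ordinary choice. Section 2.6 restricts release of results to one role, and someone must know the arms to organise classes. Nothing gives the coordinator or the list holder a part in eligibility decisions. Practitioners will see who attends a class, but nothing says they learn the order of allocation. Who screens and whether allocation is in batches are details that an article commonly leaves to the full protocol, and delivery in classes is compatible with batches. Eligibility rests mainly on two structured diagnostic interviews. The timetable criterion can be read as availability for the whole 12 weeks, and the article mentions exclusion criteria that it does not list.

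Most of this stands, and it limits the point. A reader might infer that a third of allocations are in fact known before enrolment, that the concealment statement is false, or that enrolment is being steered by arm. The article supports none of these. Each needs one-by-one allocation and a person who combines knowledge of the block size, knowledge of the preceding allocations and a say in enrolment. Nor may silence about who screens be counted as a fault.

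The objection does not remove the stated choice itself: one fixed block size, published, on one list, with results known to at least two people in a trial that is open to participants and practitioners. Under that choice, concealment depends entirely on a separation of roles that the quoted safeguards do not by themselves guarantee.

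**Conclusion.** The point holds in conditional form. If allocation is one by one, up to one allocation in three (about 21 of 64; range 0-33%) can be deduced in advance by anyone who knows the block size and the preceding allocations. Concealment is then not secured against the coordinator or the list holder if either has a part in eligibility or enrolment, which the article leaves open. Steering is a risk, not a demonstrated event. Any resulting bias runs from zero to at most 2d/3, that is up to 0.07-0.20 SD for an assumed d of 0.1-0.3 SD with every predictable slot exploited. The sample size is unaffected. The change is worth making because it is cheap.

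**What to change.** For participants not yet randomised, amend section 2.6 in one of two ways.

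1. **Preferred: allocate by cohort.** For each class cohort, complete screening, consent and T1, and confirm the timetable criterion for both class periods. Then lock the cohort and allocate all its members 1:1 in a single step. Nothing can be foreseen during screening.
2. **If allocation stays sequential:** use randomly varying block sizes that are not disclosed to site staff.

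Under either option, state that the list holder and anyone who sees past allocations take no part in eligibility decisions. Option 2 is weak without this. For participants already randomised, report who judged eligibility and what that person could know.

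**Cost.** A short amendment, reviewed by the IRB as the ethics statement requires, and a new list for the remaining participants; no extra patients or staff. Under option 1, early candidates in a cohort wait longer between T1 and the start of classes. Participants already enrolled are not protected, and with recruitment under way the number who benefit may be small.

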### Blinding

2.7

In this clinical trial, assessors will be blinded. However, participants and practitioners will not be blinded. The assessors will be blinded to the intervention group and prevented from speaking with the participants, except during the clinical interviews.

### Assessment

2.8

Assessments are scheduled at baseline (T1), post-intervention (six weeks; T2), and follow-up (12 weeks; T3). Assessments include observer ratings (conducted by blinded clinicians) and self-report ratings. A structured interview manual will be used to increase the reliability of observer ratings (e.g., 38, 39). If participants drop out, they will not be assessed further. Missing data will be statistically imputed. **Table 2** summarizes the assessment time points.

**Table 2 T2:** Study assessment points.

	Screening	T1	T2	T3
HBDIS	○			
SCID-5	○			
Demographic Information	○			
HS		○	○	○
HCT		○	○	○
HDRS		○	○	○
HARS		○	○	○
STAXI		○	○	○
IVS		○	○	○

T1, baseline; T2, post-intervention; T3, follow-up; HBDIS, Hwa-Byung Diagnostic Interview Schedule; SCID-5, Structured Clinical Interview for DSM-5; HS, Hwabyung Scale; HCT, Hwabyung Comprehensive Test; HDRS, Hamilton Depression Rating Scale; HARS, Hamilton Anxiety Rating Scale; STAXI; State-Trait Anger Expression Inventory; IVS, Integrative Vitality Scale.

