The control group in this study is a non-active group. For ethical reasons, the control group will perform MQT-SH for six weeks between the T2 and T3 assessments. Therefore, the main statistical analysis is a comparison of the two groups for T1 and T2 assessments. Additionally, a follow-up effect analysis will be conducted in the experimental group alone, and a single-arm pre-post effect analysis will be conducted in the control group. Finally, a subgroup analysis will be conducted based on the amount of home training.

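### Ending assessment of participants who attend three or fewer sessions creates avoidable missing T2 data, by attendance only in the MQT-SH arm, and can bias the main comparison

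*Protocol article*

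**What the plan says.** Three sections of the protocol article have to be read together.

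- Section 2.4.1 lists three routes to dropout. The first is attendance alone: "Dropouts will be defined as i) individuals attending three or less out of six sessions". The other two concern people who want to give up, because of discomfort or for another reason ("those who would want to give up for reasons other than discomfort"). The attendance route is separate, so it also covers people who have not asked to leave.
- Section 2.8 sets the consequence: "If participants drop out, they will not be assessed further. Missing data will be statistically imputed".
- Section 2.13 names the analysis: "Analyses based on the Intention-To-Treat (ITT) principle will be conducted, with missing data imputed using expectation-maximization (EM) algorithm". It does not say which variables enter the EM model.

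Two further statements fix where the rule acts. Section 2.4.2 says: "The control group will be assigned to WLC and will receive no treatment for the first six weeks". The Discussion says: "Therefore, the main statistical analysis is a comparison of the two groups for T1 and T2 assessments".

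**The concern.** Attendance is behaviour after randomisation. If it decides whose outcome is measured, the data go missing because of the protocol and not because of the participant. Someone who came to three sessions and would gladly attend the T2 visit is not measured, and a value predicted from other people's scores takes the place of theirs.

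The arms are also treated differently. Between T1 and T2 the wait-list arm has no sessions to miss, so the attendance criterion can remove T2 outcomes only under MQT-SH.

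What is at stake is the group-by-time comparison for every primary outcome. If low attenders benefit less than completers, and their values are predicted from MQT-SH completers, the result describes people who attended but carries an intention-to-treat label. No later analysis plan can recover scores that were never collected.

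**Working it through.** **Inputs from the protocol article.** Section 2.5: partial eta squared 0.04, power 80%, type I error 5%, 25 per group (50 in total), dropout 20%, 32 per group (64 in total). Sections 2.4.1, 2.4.2, 2.8 and 2.13: the rules quoted above.

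**Assumptions, not in the document.** Pre-post correlation 0.5 (the software default). All of the 20% dropout falls in the MQT-SH arm. Dropouts obtain a share s of the completers' benefit, with s = 0, 0.5 or 1.

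**Step 1: reproduce the plan's sample size.** f = sqrt(0.04/0.96) = 0.204. For the within-between interaction, lambda = N × f² × m/(1 - rho), with m = 2 and rho = 0.5. At N = 50, lambda = 50 × 0.04167 × 2/0.5 = 8.33, and power on 1 and 48 df is 0.8075. Inflation: 25/0.80 = 31.25, rounded up to 32 per group. Both stated figures are reproduced. The match rests on rho = 0.5: rho = 0.3 would give 68 in total and rho = 0.7 would give 32.

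**Step 2: express the planned effect as a difference in change.** In a 2 × 2 interaction the difference in change is D = 4f = 0.816 SD. At rho = 0.5 the SD of change is sqrt(2 × (1 - 0.5)) = 1, so the figure is the same in change SDs.

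**Step 3: when does the rule take effect?** After three missed sessions at most 6 - 3 = 3 can be attended. Dropout status can therefore be settled before T2.

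**Step 4: what each analysis estimates**, with q the proportion of the MQT-SH arm imputed at T2:

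- Everyone assessed: D × (1 - q(1 - s)).
- EM with arm in the model, or run within arm: D. Dropouts receive the completers' expected value.
- EM without arm: dropouts receive the pooled expected value, a fraction (1 - q)/(2 - q) of D. The estimate is D × [(1 - q) + q(1 - q)/(2 - q)]. At q = 0.20 this is D × (0.80 + 0.20 × 0.80/1.80) = 0.889 × D = 0.726 SD.

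| Dropouts' gain (q = 0.20) | Everyone assessed | EM with arm | EM without arm |
|---|---|---|---|
| none | 0.80 × 0.816 = 0.653 | 0.816 (+25%) | 0.726 (+11%) |
| half | 0.90 × 0.816 = 0.735 | 0.816 (+11%) | 0.726 (-1%) |
| equal | 0.816 | 0.816 (0%) | 0.726 (-11%) |

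**Step 5: simulation check** (4,000 runs, 32 per arm). Here 20% rounds to 6 of 32, or 18.75%, so with no gain the target is 0.816 × 26/32 = 0.663. For gains of none, half and equal, the means were 0.66, 0.74 and 0.81 with everyone assessed, 0.82, 0.82 and 0.81 for EM with arm, and 0.73, 0.73 and 0.72 for EM without arm. With 20% dropout in both arms and no gain in MQT-SH dropouts, the three means were 0.65, 0.81 and 0.66.

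**Step 6: other dropout rates.** With no gain in dropouts and arm in the model, the overstatement factor is 1/(1 - q): 1.11 at 10%, 1.25 at 20% and 1.43 at 30%.

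**Step 7: power if low attenders are assessed.** With 20% of the MQT-SH arm gaining nothing, f falls to 0.80 × 0.204. At N = 64, lambda = 64 × 0.04167 × 0.64 × 2/0.5 = 6.83 and power is about 0.73. It is 0.83 at 10% and 0.61 at 30%.

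**The case against.** The strongest reply is that the direction of bias is not established. A reader might infer that the rule certainly overstates the effect. That needs two conditions: low attenders must benefit less than completers, and EM must use arm. The article fixes neither, and the choice of EM variables is a detail that an article may leave to a fuller plan. The table shows no bias with equal benefit, and downward bias if EM also omits arm. This stands. Less benefit in low attenders is still the natural expectation if the training works, and section 2.13 itself plans to compare effects by amount of home training.

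Other stronger readings also go too far:

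- *That those imputed are exactly the people who did not take up the training.* Someone who attended three sessions may have completed the whole first module (sessions 1 to 3). People who give up for other reasons, including controls, are imputed too. Zero benefit is a worst case.
- *That the 25% measures the harm of the attendance rule.* The planned 20% is total dropout, and section 2.5 applies it to both groups. The part due to attendance is not given, and people who refuse assessment stay missing under any rule.
- *That no imputation from observed scores could remove the bias.* If dropouts gain nothing, imputing them from the control arm targets the 0.653 SD of the table.
- *That section 2.13 flatly contradicts intention-to-treat.* Randomised participants are kept and missing outcomes imputed, which is common practice. The fair complaint is that the missingness is avoidable.

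None of this justifies withholding an assessment that a participant would accept.

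**Conclusion.** The point holds in this form: followed as written, sections 2.4.1 and 2.8 create avoidable missing T2 data for low attenders, the attendance criterion does so only in the MQT-SH arm before T2, and the main comparison can be biased as a result. Bias in favour of MQT-SH is probable if low attenders benefit less, but the document does not demonstrate it.

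With 20% dropout in the MQT-SH arm only, the illustrated bias runs from 0% to +25% if EM uses arm and from about -11% to +11% if it does not. These figures rest on the correlation of 0.5 that reproduces the plan's sample size and on the assumed gain of dropouts. They illustrate the possible size and do not predict it. The planned sample size is not itself in error here.

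This should be corrected while visits remain, because it touches every primary outcome and uncollected scores cannot be restored at analysis.

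**What to change.** Replace the sentence in section 2.8 with wording such as: *Every randomised participant is invited to the T2 and T3 assessments whatever the number of sessions attended. Assessment stops only if the participant withdraws consent to assessment.* Keep the three-session rule only as the definition of non-adherence for a secondary analysis. Impute only outcomes that could not be obtained.

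Section 3.3 says that treatment has begun, so some T2 assessments may already have been missed. For these, and for refusals, add a sensitivity analysis that imputes MQT-SH dropouts from the control arm.

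The costs are modest but not nil. The amendment needs IRB review under the Ethics statement. Some assessments that would have been cancelled are carried out; T2 and T3 are already scheduled for every participant, but the article gives no budget. The estimate may be smaller once low attenders are measured: if 20% of the MQT-SH arm gain nothing, power at N = 64 is about 0.73, below the planned 80%. That is the price of estimating the effect in everyone randomised.
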